## Abstract

Background: This study aims to investigate the relationship between muscle activation variables assessed via ultrasound and the comprehensive assessment of geriatric patients, as well as to analyze ultrasound images to determine their correlation with morbimortality factors in frail patients.

Methods: The present cohort study will be conducted in 500 older adults diagnosed with frailty. A multicenter study will be conducted among the day care centers and nursing homes. This will be achieved through the evaluation of frail older adults via instrumental and functional tests, along with specific ultrasound images to study sarcopenia and nutrition, followed by a detailed analysis of the correlation between all collected variables.

Discussion: This study aims to investigate the correlation between ultrasound-assessed muscle activation variables and the overall health of geriatric patients. It addresses the limitations of previous research by including a large sample size of 500 patients and measuring various muscle parameters beyond thickness. Additionally, it aims to analyze ultrasound images to identify markers associated with higher risk of complications in frail patients. The study involves frail older adults undergoing functional tests and specific ultrasound examinations. A comprehensive analysis of functional, ultrasound, and nutritional variables will be conducted to understand their correlation with overall health and risk of complications in frail older patients.

Trial registration: The study was approved by the Research Ethics Committee of the Hospital Universitario Puerta de Hierro, Madrid, Spain (Act nº 18/2023). In addition, the study was registered with https://clinicaltrials.gov/ (NCT06218121).

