### Materials

Measurement variables evaluated in patients include:

Manual grip strength: The peak grip force was measured using a hydraulic hand dynamometer (JAMAR, Sammons Preston Rolyan, Sammons Court Bolingbrook, IL, USA) across a range of 0 to 90 kg. This device has been validated, shown to be reproducible, and deemed reliable for assessing grip strength in older individuals [22].Quality of life: measured with the EuroQol-5D, where mobility, personal care, daily activities, pain/discomfort, anxiety, or depression are assessed [23].Barthel Index: Assesses the level of independence of the subject with respect to the performance of activities of daily living [24].Trunk control test: Designed for the assessment of the patient's motor impairment [25].Intensity of Pain: Using the NPRS [26].Ultrasound image: The cross-sectional area and thickness of the rectus femoris muscle will be measured. In addition, contraction potential, contraction-relaxation velocity data will be taken by M-Mode ultrasound [27].The State-Trait Anxiety Inventory (STAI): Assessing state and trait anxiety [28].Kinesiophobia (TSK): Using the Tampa Kinesiophobia Scale, measuring fear of movement [29].Beck Depression Inventory (BDI): It measures depressive symptoms and the severity of depression [30].

Figure 1 illustrates the collection of variables in the older adult population of the study. Figure 2 summarizes the study workflow, from participant recruitment and assessments to the machine learning pipeline for prediction and analysis.

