### Statistical analysis

The R program version 4.3.1 will be used for statistical analysis. The level of significance will be set at *p* < 0.05. The distribution of quantitative variables, both baseline and outcome, will be tested with the Kolmogorov-Smirnov test with Lilliefors correction. Qualitative variables will be described in absolute values and frequencies and quantitative variables with mean and standard deviation.

Baseline and outcome variables differences using Barthel Index (BI) score dichotomized between dependent (BI < 60) and independent (BI > 60) patients [31] using *T*-test or U-Mann-Whitney for quantitative variables (depending on their distribution) and Fisher exact test for qualitative variables.

A multivariate analysis will be performed with a machine learning model through principal analysis using logistic regression, applying the model to 75% of the subjects and evaluating its accuracy in the remaining 25%, with the objective of creating a trained model that allows the development of therapeutic intervention plans that enable both the evaluation and treatment of patients. Model will be controlled by baseline variables with significant differences in univariate analysis.

Model will be constructed with dichotomized Barthel index as dependent variable and manual grip strength, EuroQoL-5D, NPRS, cross sectional area and thickness of the rectus femoris, STAI, TSK and BDI as explanatory variable. Logistic model will be selected instead of others used in machine learning (e.g. Random Forest, Support Vector Machines or Gradient Boosting) because it is computationally more efficient and faster and more easily interpretable.

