### Cost-effectiveness evaluation

Given the research design, we will seek to compare the cost of using ultrasound vs. battery of tests, although we assume that the use of battery of tests will be more economical.

A secondary analysis will be performed that will mainly include the following elements of analysis to complete an economic evaluation of both alternatives:

Resource consumption and costs involved in both alternatives.Using if possible, a social approach, differentiating it from the approach of the funder (Public Health Service).Include a sensitivity analysis of the most influential variables on the results.

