### Sample size calculation

The sample size was carried out based on the main objective and analysis of the study to evaluate which variables influence the level of dependence/independence through a multivariate logistic regression model, with Barthel index dichotomize as dependent variable, and manual grip strength, EuroQoL-5D, NPRS, cross sectional area and thickness of the rectus femoris, STAI, TSK and BDI as explanatory variable, for which a sample of 500 subjects was recommended according to Bujang et al. formula (100 + 50 × number of explanatory variables) and minimum sample size for logistic regression models [38–40].

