## DISCUSSION

The aim of this study is twofold: firstly, to investigate the correlation between muscle activation variables assessed via ultrasound and the comprehensive assessment of geriatric patients. This approach seeks to better understand how ultrasound findings may be related to the overall health and functional status of older patients. In addition, lastly published review found that ultrasound showed a low-to-moderate diagnostic test accuracy for sarcopenia, although included sample sizes was low (most studies less than 200 patients) and mostly only measured muscle thickness [41]. To counteract these limitations, this study has a large sample size with 500 patients and will measure muscle thickness but also cross-sectional area, as well as contraction potential and contraction-relaxation velocity with M-mode. Secondly, to analyze ultrasound images using histogram distribution to determine their correlation with mobi-mortality factors in frail patients. This approach will identify potential ultrasound markers that may be associated with a higher risk of complications in frail patients, as other studies found in the literature [42, 43].

To achieve these objectives, a study will be conducted on frail older adults, who will undergo a series of instrumental and functional tests designed to assess their functional capacity. Additionally, specific ultrasound images will be obtained to study sarcopenia and nutrition in this patient group. Subsequently, a comprehensive analysis of the correlation between all functional, ultrasound, and nutritional variables collected during the study will be conducted. This analysis will identify potential relationships between muscle activation, ultrasound image, and overall health and risk of complications in frail older patients.

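### The analysis designated as main leaves out the M-mode and grey-level variables behind the two stated aims, and its single combined model does not show what ultrasound adds to the clinical battery

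*Protocol article*

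**What the plan says.** **Aims.** The Abstract intends to "investigate the relationship between muscle activation variables assessed via ultrasound and the comprehensive assessment of geriatric patients". The Discussion repeats this and gives the second aim as to "analyze ultrasound images using histogram distribution to determine their correlation with mobi-mortality factors in frail patients".

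**What is measured.** Materials lists rectus femoris area and thickness, and adds that "contraction potential, contraction-relaxation velocity data will be taken by M-Mode ultrasound". The muscle architecture section also includes an M-mode image for contraction potential and relaxation velocity. The Discussion presents these M-mode measures, together with cross-sectional area, as an advance on earlier studies that mostly recorded thickness alone. Image analysis lists first-order grey-level statistics and several families of texture features.

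**What is analysed as main.** Sample size calculation bases N on the "main objective and analysis of the study to evaluate which variables influence the level of dependence/independence". Statistical analysis says "Model will be constructed with dichotomized Barthel index as dependent variable". The predictors are grip strength, EuroQoL-5D and NPRS, followed by "cross sectional area and thickness of the rectus femoris, STAI, TSK and BDI as explanatory variable". Both sections give the same list.

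**How the model is judged.** The modelling steps are removal of variables with VIF above 5, elastic-net selection, and then AUC, sensitivity/specificity, F1 and variable importance for one model.

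**Other analyses.** Samples promises correlations among all functional, ultrasound, nutritional and psychological variables. "The level of significance will be set at" p < 0.05, and no multiplicity adjustment is mentioned.

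**The concern.** The aims concern muscle activation and image grey levels. The analysis that carries the label of main objective, and that justifies the number of patients, concerns neither. It asks which variables go with dependence, and ultrasound enters only through two size measures. The measures that the Discussion offers as part of the study's contribution thus have no place in the confirmatory part of the plan.

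Ultrasound and clinical tests also enter one model together. Its AUC describes the mixture. A good AUC could come entirely from grip strength and EuroQoL-5D, and the report could not say whether scanning the patient improved on the questionnaires and the dynamometer.

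The image features raise a smaller, conditional worry. There are many of them, the stated purpose is to find markers, and the only threshold given is a flat p < 0.05.

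**Working it through.** **1. The plan's own sample size.** The rule under Sample size calculation is n = 100 + 50k, where k is the number of explanatory variables. With the eight listed predictors, 100 + 50 × 8 = 500. The stated figure is reproduced exactly, so N = 500 belongs to that list.

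**2. Predictors set against the aims.**

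| Source | Predictors in the main model | Count |
|---|---|---|
| Clinical battery | grip, EuroQoL-5D, NPRS, STAI, TSK, BDI | 6 |
| Ultrasound, muscle size | rectus femoris area, rectus femoris thickness | 2 |
| Ultrasound, M-mode activation (aim 1) | none | 0 |
| Ultrasound, grey-level features (aim 2) | none | 0 |

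**3. The same rule with M-mode added.** Contraction potential and contraction-relaxation velocity count as two variables, or three if contraction and relaxation velocities are separate.
- k = 10: 100 + 50 × 10 = 600
- k = 11: 100 + 50 × 11 = 650

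**4. Does the model show what ultrasound adds?** The steps produce one fitted model and one set of performance figures. Variable importance ranks terms within that model; it does not compare performance with and without ultrasound. Area and thickness describe the same muscle, so the VIF rule could remove one of them, and the elastic net could remove what is left. The final model might then contain no ultrasound term at all.

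**5. Image features.** Counting the list under Image analysis: 5 first-order + 18 GLCM + 7 GLRLM + 1 LBP + 3 blob = 34. With the four directions kept separate for GLCM and GLRLM: 5 + 4 × (18 + 7) + 1 + 3 = 109.

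If each of the 34 is tested once against one outcome at 0.05 with no true association, the expected number of false positives is 0.05 × 34 = 1.7, whatever the correlation among features. With 109 it is 0.05 × 109 = 5.45.

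The chance of at least one is 1 − 0.95^m, where m is the effective number of independent tests:

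| m | Chance of at least one |
|---|---|
| 5 | 0.226 |
| 10 | 0.401 |
| 20 | 0.642 |
| 34 (full independence) | 0.825 |

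The last row is an upper illustration. The list includes both standard deviation and variance, and texture features from one region are related. The effective number is not known from the article, so 5 to 20 is an assumed range.

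**6. What correction would cost.** Using Fisher's z, two-sided (assumed), 80% power and N = 500, the detectable correlation is r = tanh[(z₁₋α/₂ + z₀.₈)/√497]. At α = 0.05, r = 0.125. At the Bonferroni level 0.05/34 = 0.00147, r = 0.178. Even that stricter correction leaves modest correlations within reach.

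**The case against.** - **A reader might infer that the main analysis cannot answer the study's question.** The article does not support this. The aims are worded as correlations, and Samples plans correlations across all ultrasound and clinical variables. The logistic model does address the objective that the sample size section sets for it. What remains is that two sections name different main purposes, and the aims in the Abstract and Discussion are served only outside the designated analysis.
- **The aims name neither M-mode nor texture.** True. The link comes from Materials, Image analysis and the Discussion. It is firm for M-mode, since no other collected ultrasound measure describes activation. It is looser for the second-order texture features, because the Discussion speaks of histogram distribution.
- **The model's ultrasound terms are not merely old measures.** This stands. The Discussion counts cross-sectional area among the study's advances.
- **Other variables could enter.** The model is to be adjusted for baseline variables that differ significantly in univariate analysis. That might admit M-mode terms, but only by data-driven screening and beyond the eight predictors behind N = 500.
- **No stated objective is to estimate the added value of ultrasound.** Correct. The nested comparison is therefore an improvement and not the repair of an error, though it serves the declared wish to improve ultrasound diagnosis.
- **No sentence assigns each image feature a test at p < 0.05.** Also correct, and an unseen analysis plan could hold a correction. The multiplicity part is conditional.
- **A reader might also infer that the ultrasound-versus-battery cost comparison is defective for want of an effect measure.** A condensed article may leave that detail to a fuller document, so it is not part of this point.

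**Conclusion.** The mismatch holds on the text. The eight predictors that give N = 500 include no M-mode and no grey-level variable, while both aims rest on such variables. An unseen analysis plan would not remove the conflict between the aims in the Abstract and Discussion and the main objective in the sample size section. The single combined model also gives no with-and-without comparison for ultrasound.

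The stated N is not arithmetically wrong; it covers the listed model only. By the protocol's own rule, adding the M-mode terms corresponds to 100 to 150 more patients than planned.

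The multiplicity element is secondary and conditional on the features being tested individually at 0.05. Then 1.7 false positives are expected per outcome under the null. The chance of at least one is about 23% to 64% for 5 to 20 effective tests, and reaches 83% only under an independence that does not apply here.

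This should be corrected, but it does not invalidate the study.

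**What to change.** 1. **Reconcile the objectives.** Make the main objective in Sample size calculation agree with the aims in the Abstract and Discussion, or state that the Barthel model is the main analysis and that the activation and image aims are secondary.
2. **Pre-specify a secondary nested comparison on the same patients.** Model A: the clinical battery only (grip, EuroQoL-5D, NPRS, STAI, TSK, BDI). Model B: the same plus area, thickness and the M-mode variables. Report the change in cross-validated or optimism-corrected AUC. Add a likelihood-ratio test only if both models are fitted unpenalised, because the standard test does not apply to elastic-net fits.
3. **Keep N = 500 and say what it was sized for.** State that it comes from eight predictors, and that the same rule would give 600 for ten and 650 for eleven.
4. **Label the image features exploratory.** If they are tested, treat them as one family with false-discovery-rate control, and say whether directions are averaged or kept separate.

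The cost is wording and a few extra fits on data already to be collected, with no added recruitment. The small downside is that the extended model will be less precise than the rule intends at 500, which the report should say.

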## BACKGROUND

### The concept of frailty

Between 2015 and 2050, the global population aged 60 and above is projected to rise from 12% to 22% [1]. Advancing age correlates with a higher incidence of chronic ailments, frailty, dependency, and elevated healthcare expenditures [2–4]. Frailty is a complex medical condition marked by diminished strength, endurance, and physiological functions, heightening an individual's susceptibility to adverse outcomes, including mortality [5]. Its prevalence among the elderly ranges from 8% to 16% and is often intertwined with dementia [6] or cardiovascular disease [7]. Moreover, frailty in older adults frequently coexists with sarcopenia, an age-related syndrome characterized by progressive muscle mass and strength decline, heightening the risk of physical impairment and diminished quality of life [8].

### Pathophysiology of frailty and sarcopenia

Inflammaging presents a theory regarding frailty, suggesting that as individuals age, they experience a continuous low-level inflammation characterized by the release of proinflammatory cytokines from aging organs [5]. Individuals exhibiting frailty often display elevated levels of Interleukin-6 (IL-6), C-reactive protein (CRP), and Tumor Necrosis Factor-alpha (TNF-α), partially attributed to the prevalence of overweight/obesity in the elderly population. Moreover, frail individuals typically exhibit compromised immune function, diminished antibody production, or heightened mitochondrial oxidative stress, resulting in increased levels of inflammatory markers [5].

Individuals with sarcopenia commonly demonstrate heightened concentrations of biomarkers like CRP, Interleukin-1β (IL-1β), IL-6, or Interleukin-8 (IL-8), fostering a milieu of chronic inflammation. This condition is also associated with disruptions in amino acid metabolism and intestinal dysbiosis, leading to increased intestinal permeability to various microbes or their byproducts, subsequently triggering inflammatory responses and immune system dysregulation [9]. This sustained state of inflammation, coupled with hormonal shifts and other physiological processes, ultimately contributes to mitochondrial dysfunction within muscles, accelerated apoptosis of myonuclear cells, and impaired function of muscle satellite cells, culminating in muscular weakness [10].

### Diagnostic methods of frailty and sarcopenia

Various tools are employed for diagnosing frailty, including the “frailty phenotype,” which assesses weakness, slowness, exhaustion, low physical activity levels, and weight loss. Pre-frailty is recognized with the presence of one or two of these criteria, while frailty requires three or more [11, 12]. Other diagnostic approaches include the Frailty Index, Clinical Frailty Scale, or FRAIL scale [13].

Sarcopenia diagnosis hinges on low muscle strength, reduced muscle quantity/quality, and diminished physical abilities. Probable sarcopenia is diagnosed if the first criterion is met, sarcopenia if both the first and second are present, and severe sarcopenia if all three criteria are satisfied [14]. Additionally, assessment tools such as SARC-F questionnaires, muscle strength tests, diagnostic procedures like dual-energy X-ray absorptiometry (DXA), or physical assessments such as gait speed tests are employed [14].

DXA imaging allows quick determination of muscle tissue quantity, setting thresholds at <5.5 kg/m^2^ for women and <7.23 kg/m^2^ for men, with minimal radiation exposure and lower costs compared to computed tomography. However, DXA's efficacy is limited by low specificity and inability to assess muscle quality regarding fatty infiltration [15]. Computed tomography is the gold standard for evaluating muscle mass and quality but carries risks due to radiation exposure [15].

Ultrasound has emerged as a promising tool for diagnosing muscle conditions like frailty and sarcopenia, demonstrating comparable efficacy to DXA in assessing muscle mass and excellent reliability (ICC >0.9). Analysis of echo intensity in ultrasound images allows inference of muscle tissue quality [16]. The International Society of Physical Medicine and Rehabilitation has proposed an ultrasound-based algorithm for evaluating muscle mass, utilizing muscle thickness relative to body mass index, with loss of body mass defined as values <1 for women and <1.4 for men when comparing past and current measurements [16].

### Relevance and justification

Despite considerable research on frailty and sarcopenia in recent years, the prevalence of these is on the rise due, in part, to the growth of the elderly population and an increase in sedentary lifestyle among the elderly population. Current diagnostic methods such as DXA or Computed Tomography (CT) are expensive and involve radiation risk. Other methods, such as the FRAIL scales or the Clinical Frailty Scale, may require time and adequate patient cognition to perform. Faced with this dilemma, ultrasound has emerged as a method for evaluating muscle quality and quantity, being recommended by international organizations for use in the evaluation of frailty.

The correlation of the demographic variables, physical functionality tests and psychoemotional constructs that will be analyzed in this study with the ultrasound image obtained from the patients will improve the ultrasound diagnosis of frailty, providing new information that will facilitate the work of healthcare personnel in the diagnosis and management of frailty.

Similarly, the use of Machine Learning will allow institutions to extract data on different patient profiles, signs and symptoms of frailty and the different risk factors that affect frailty patients, which will improve treatments and favor the development of educational programs tailored to the patient's needs.

### Objectives

In this context, we designed the study to assess:

Update the diagnostic assessment of frailty by correlating several variables with the ultrasound image of the frail elderly patient.We intend to collect and analyze data on functional capacity and quality of life variables on the evolution of musculoskeletal symptoms, as well as on pain and psychological variables. Similarly, it is intended to make a record of different profiles and subtypes of frail older adult patients to be stored with Machine Learning in order to establish therapeutic intervention plans that allow both the evaluation and treatment of patients.

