### Samples

A diagnosis of signs and symptoms of frailty by a geriatric physician from the research group ([name]) and the centers' medical staff will be used as the main inclusion criterion. Frailty will be assessed and diagnosed using the frailty phenotype and the Clinical Frailty Scale.

As exclusion criteria:

Acute myocardial infarction in the last 3 months and/or unstable angina pectoris.Uncontrolled arrhythmia, recent thromboembolism, and terminal illness.Patients with recent unloading of lower limbs (LL), or with UL/LL fractures in the last three months.Patients with a functional gait index of 1 (Inability to walk).Severe pain (7/10 Numeric Pain Rating Scale, NPRS).Previous neuromuscular pathology presenting with weakness.Medication that does not allow the patient's actual muscle reaction to be assessed.Severe cognitive impairment that would prevent collaboration and understanding of the tests to be performed.Cardiovascularly unstable patients and uncontrolled arterial hypertension.

For the cohort study, 500 frail older adult patients will be evaluated by means of instrumental and functional tests that assess their functional capacity, in addition to ultrasound imaging to study sarcopenia and nutrition, as well as psychological variables. The correlation between all functional, ultrasound, nutritional, and psychological variables will be analyzed. Through the Global Leadership Initiative on Malnutrition (GLIM) criteria diagnosis, anthropometric data (weight, height, and Body Mass Index-BMI) as well as analytical data including inflammation information (CRP and albumin) will be used to reach a diagnosis that allows comparison/correlation with the rest of the variable parameters [18]. The GLIM criteria provide a diagnostic system that has been accepted by the main international scientific societies in the field of clinical nutrition [19–21]. All available information will be collected during the follow-up in order to generate Machine Learning on the objective evolution and symptomatology of these patients, generating profiles that facilitate the most accurate and appropriate treatment for each patient.

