All sonographic images will be obtained in a standardized position: participants seated with 90° hip and knee flexion, and the probe placed perpendicularly at the distal third of the thigh, as marked based on femur length. Water-based transmission gel will be used to avoid pressure artifacts. The acquisition protocol includes three sagittal plane images of the vastus lateralis, and a fourth M-mode image to assess contraction potential and relaxation velocity. All ultrasound operators were blinded to the frailty classification of the participants during image acquisition. The reproducibility of ultrasound measurements was confirmed during a pilot study prior to data collection, with intra- and inter-rater intraclass correlation coefficients (ICC) exceeding 0.90 for both muscle thickness and cross-sectional area, indicating excellent agreement.

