### Implications and limitations

The potential implications of this study are substantial for both clinical practice and public health. The integration of ultrasound-derived muscle parameters with functional and psychological assessments, analyzed through machine learning, offers a scalable and cost-effective approach for the early detection of frailty. This may enable clinicians to stratify risk and tailor interventions in community-dwelling and institutionalized older adults, enhancing preventive care and reducing adverse outcomes associated with frailty.

Nonetheless, the study presents several limitations. First, the ultrasound measurements are operator-dependent, which introduces a risk of inter-rater variability. To mitigate this, we ensured strict standardization of procedures and training across all sites, along with reliability testing. Second, although the machine learning model will be internally validated using cross-validation and a separate test set, no external validation in a different population is planned in this protocol. Third, as participants are recruited by convenience sampling from institutional settings, there is a potential for selection bias and limited generalizability to broader older adult populations. Fourth, the accuracy of ultrasound imaging can be affected by the presence of subcutaneous fat, particularly in individuals with overweight or obesity. Excess adipose tissue may reduce image clarity, impairing precise delineation of muscle boundaries and affecting measurements of thickness and cross-sectional area. To address this limitation, we use a standardized acquisition protocol with high-frequency probes and minimal compression, and we plan to include anthropometric indicators such as body mass index (BMI) in the analysis to statistically adjust for this potential confounder. Lastly, while the current model focuses on predicting dependence based on the Barthel Index, other frailty dimensions (e.g., cognitive, social) may not be fully captured. These limitations will be addressed in future longitudinal studies with broader inclusion criteria and external validation.

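### The objective promises progress in diagnosing frailty by ultrasound, but every participant is frail and no stated analysis contains a frailty measure

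*Protocol article*

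**What the plan says.** The first aim under Objectives is to "Update the diagnostic assessment of frailty by correlating several variables with the ultrasound image of the frail elderly patient". Relevance and justification says that correlating demographic, functional and psychoemotional variables with the image "will improve the ultrasound diagnosis of frailty". Implications and limitations adds that the approach offers a route to detecting frailty early.

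Under Samples, a geriatric diagnosis of frailty "will be used as the main inclusion criterion", and "Frailty will be assessed and diagnosed using the frailty phenotype and the Clinical Frailty Scale". Muscle architecture processing and analysis states: "All ultrasound operators were blinded to the frailty classification of the participants during image acquisition".

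The analyses are built on something else. Under Statistical analysis, groups are compared by Barthel Index below or above 60, and "Model will be constructed with dichotomized Barthel index as dependent variable". Sample size calculation calls this dependence model the study's main objective and analysis. Implications and limitations concedes that "the current model focuses on predicting dependence based on the Barthel Index" and that other dimensions of frailty may be missed.

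**The concern.** To say something about diagnosing a condition, a study needs either people with and without it or, failing that, a measure of its degree. This cohort has no people without frailty, and the stated analyses use no measure of its degree. What remains is the relation of ultrasound to dependence in daily living, and to function, nutrition, pain and mood, among people who are all frail. Dependence is related to frailty but is not the same construct.

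At stake is interpretation. If the plan is followed as written, a model that separates dependent from independent frail patients could be published under an objective about diagnosing frailty, and its AUC, sensitivity and specificity read as diagnostic accuracy for frailty. They would be nothing of the kind.

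**Working it through.** **1. The plan's own figure.** Sample size calculation gives 100 + 50 × number of explanatory variables. The variables listed are grip strength, EuroQol-5D, NPRS, rectus femoris area, rectus femoris thickness, STAI, TSK and BDI, which makes 8. Then 100 + 50 × 8 = 500, as stated. None of the eight is a frailty measure and the outcome is Barthel dependence, so the study is sized for dependence.

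**2. Each stated analysis, checked for a frailty variable.**
- Group comparisons (Statistical analysis): groups defined by Barthel Index; no frailty grade named.
- Logistic model with elastic net (Statistical analysis): outcome is Barthel, with the eight predictors above; no frailty grade named.
- Correlations (Samples): functional, ultrasound, nutritional and psychological variables; frailty not listed.
- Image analysis (Discussion): image features against morbidity and mortality factors; frailty not the target.
- Cost comparison (Cost-effectiveness evaluation): ultrasound against the test battery; no frailty outcome.

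Result: 0 of 5.

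**3. Is a graded measure available?** The phenotype is a count. Diagnostic methods of frailty and sarcopenia lists five criteria and says: "Pre-frailty is recognized with the presence of one or two of these criteria, while frailty requires three or more". If that cut-off is the entry rule (Samples does not restate it), participants can score 3, 4 or 5. The article does not list the levels of the Clinical Frailty Scale. Neither tool is in the variable list under Materials or in Table 1. The assessment is therefore made at entry, but nothing in the article assures that the grade is kept as study data.

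**4. What 500 patients would give for a severity question.** For a single unadjusted correlation, two-sided 5% (sidedness assumed) and 80% power, the smallest detectable value is tanh((1.96 + 0.8416)/√(500 − 3)) = tanh(0.1257) = 0.125. This is a best case. Restricting the range to frail people shrinks the observable correlation to R·u/√(1 − R² + R²u²), where u is the ratio of restricted to unrestricted SD. The article gives neither R nor u. Assuming R = 0.30:
- u = 0.4: 0.12/√0.9244 = 0.125
- u = 0.6: 0.18/√0.9424 = 0.185
- u = 0.8: 0.24/√0.9676 = 0.244

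At the low end, the observable correlation sits right at the best-case limit, before any loss from covariates, tied grades or clustering by centre.

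**The case against.** The strongest reply is that the objective states its own method, correlating several variables with the ultrasound image, and that Samples plans exactly those correlations. This stands in part. A reader might infer that none of the planned results bears on the first objective, and the article does not support that: the correlations carry out the named method. What they cannot do, in an all-frail sample and without a frailty variable, is support a conclusion about how frailty is diagnosed.

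Second, the choice of Barthel is open. Sample size calculation names dependence as the main objective, and Implications and limitations admits the model's focus. That is fair, but the admission treats dependence as one dimension of frailty and leaves the objective unchanged, and the same section still claims early detection.

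Third, the generic baseline variables under Statistical analysis could include a frailty grade. It is not named there. It would at most be compared between Barthel groups or enter as a covariate, which does not address diagnosis.

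Fourth, an extra regression could be left to an analysis plan that is not shown. That would answer a complaint about missing detail. Here the article itself fixes the outcome, the predictors and the sample size basis of its main analysis, and these do not match its stated objective.

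**Conclusion.** The mismatch between objective and analyses holds. Ultrasound is related to dependence and to functional, nutritional and psychological variables, and in no stated analysis to frailty. The design can show associations among frail older adults. It cannot show diagnostic performance for frailty. This rests on the article's text alone: frailty as the entry condition, and the outcome and predictors it names. The Barthel model remains a legitimate analysis of dependence.

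Two stronger readings should be avoided. One is that frailty grades are already in the database and merely unused. The article says the two tools are applied at entry, not that their grades are recorded. The other is that 500 patients give 80% power to detect a correlation of 0.125 with frailty grade in the analysis recommended here. That figure is arithmetically right for one unadjusted correlation, but it is not the power of an adjusted ordinal model over a truncated range of grades, and should not be quoted as such. Precision will be poorer, by an amount the article does not allow one to calculate.

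**What to change.** 1. Reword the first objective, and the early-detection claim under Implications and limitations, to what the design can show: association of ultrasound measures with dependence, and with severity of frailty, among frail older adults. This brings them into line with the main objective in Sample size calculation.

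2. Add the Clinical Frailty Scale level and the phenotype criterion count to the variable list under Materials and to Table 1, so that the entry assessments are kept as study data.

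3. Pre-specify one secondary ordinal regression of Clinical Frailty Scale level on named ultrasound measures, adjusted for age, sex, BMI and centre, with the phenotype count as a sensitivity outcome. Adjustment for BMI is already intended under Implications and limitations.

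The cost is two recorded fields, one secondary analysis and some rewording. Recruitment and the main model do not change, because frailty enters as a separate outcome. Adding it to the main model as a ninth predictor would instead raise the plan's own rule to 100 + 50 × 9 = 550. For anyone already enrolled, the grades would have to be retrieved from the entry assessment. The downside is that the range is confined to frail grades, so the result informs severity and not a diagnostic cut-off. Report it as estimates with confidence intervals, without a power claim.
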